## **5. TREATMENT OF SUBJECTS**

All children in group 2 follow the standard NIP (they have or will receive vaccinations with Synflorix®, a ten-valent pneumococcal conjugate vaccine (PCV10) and DTaP-IPV-Hib-HepB, at the age of 2, 3, 4 and 11 months), which is not part of this study.

### **5.1 Investigational product/treatment**

All children in group 1 will receive Prevenar-13® instead of PCV10. For the rest they will follow the standard NIP, at the age of 2, 3, 4 and 11 months. All vaccinations (PCV13 and DTaP-IPV-Hib-HepB) are given by the study team in order to prevent vaccine mix-up during well-baby clinic appointments. The DTaP-IPV-Hib-HepB is not part of this study, but will be given by the study team for practical reasons.

There is no placebo group present in this trial.

### **5.2 Use of co-intervention (if applicable)**

There is no objection against the use of co-medication or other kinds of interventions against concomitant disorders. The use of painkillers against local pain after vaccination is also not prohibited. Use of immunosuppressive medicines during the trial could in certain cases lead to exclusion of the corresponding blood samples for further laboratory analysis, since that might interfere with the outcomes of the study. Medicine use will be recorded in the questionnaire and the CRF.

### **5.3 Escape medication (if applicable)**

For blood collection a local anesthetic (Emla® crème; AstraZeneca) will be used to minimize the pain.

For vaccination normal NIP practices will be followed.

## 6. INVESTIGATIONAL MEDICINAL PRODUCT

In this trial **Prevenar-13®**, a thirteen-valent pneumococcal vaccine (PCV13), is used.

Synflorix®, a ten-valent pneumococcal vaccine (PCV10) is not administered in the trial, since children receive this vaccine as part of the NIP. However, we intent to look at the outcome of these vaccinations and therefore we included the information of PCV10 in chapter 6.1-6.4.

### 6.1 Name and description of investigational medicinal product(s)

**PCV13:** For the qualitative and quantitative composition see chapter 2 and 6.1 of the SPC.

**PCV10:** For the qualitative and quantitative composition see chapter 2 and 6.1 of the SPC.

### 6.2 Summary of findings from non-clinical studies

**PCV13:** See chapter 5.3, page 12 of the SPC.

**PCV10:** See chapter 5.3, page 9 of the SPC.

### 6.3 Summary of findings from clinical studies

**PCV13:** See chapter 5.1, page 7-11 of the SPC.

**PCV10:** See chapter 5.1, page 7-9 of the SPC.

### 6.4 Summary of known and potential risks and benefits

**PCV13:** See chapter 4 and 5, page 2-12 of the SPC.

**PCV10:** See chapter 4 and 5, page 2-9 of the SPC.

### 6.5 Description and justification of route of administration and dosage

**PCV13:** The vaccine with a dosage of 0.5 ml will be administered i.m., as prescribed by the supplier (Wyeth).

## **6.6 Dosages, dosage modifications and method of administration**

**PCV13:** The dosage of use is 0.5 ml.

During storage, a white deposit and clear supernatant can be observed. The vaccine should be shaken well to obtain a homogeneous white suspension prior to expelling air from the syringe, and should be inspected visually for any particulate matter and/or variation of physical aspect prior to administration. Do not use if the content appears otherwise.

## **6.7 Preparation and labelling of Investigational Medicinal Product**

**PCV13:** The normal packaged vials contain 0.5 ml vaccine, as supplied by the manufacturer Wyeth. The vaccine is obtained from Wyeth by the RIVM (RCP/IOD). The vaccine should be withdrawn from the vial *lege artis* into the syringe for i.m. injection.

## **6.8 Drug accountability**

**PCV13:** The appropriate number of vaccines are received from the RIVM (RCP/IOD) and stored in a dedicated study fridge. The transfer from the RCP/IOD to the study team will be documented.

All vaccines taken from the fridge by the study team will be documented. The investigator/study team member is responsible for the correct transport and storage conditions to the location of vaccination. The vaccines are transported in isolated coolers that demonstrate the adequate temperature. The vaccine may not be frozen.

In case of unusable vaccines, e.g. vials that are expired or damaged, the vaccine will be returned to the RIVM (RCP/IOD) and replaced.

Each vaccine delivery has to be accompanied with signed receipt form containing information about quantity, expiry date and batch numbers of the supplied vaccines. The form needs to be dated and signed by the person responsible for the transport and the person receiving the product. The investigator is responsible for the accountability in the fridge. If discrepancies are observed between the number of delivered and used vaccines at the end of the study, a written declaration has to be supplied by the investigator. All unused vaccines should be returned to the RIVM (RCP/IOD) at the end of the study.

## 7. METHODS

### 7.1 Study parameters/endpoints

#### 7.1.1 Main study parameter/endpoint

##### *Pneumococcal serotypes*

- Cellular immune response (Plasma B cells and memory B cells) immediately before and 7-9 days after the booster at 11-months of age
- Humoral immune response (antibody concentrations and geometric mean concentrations (GMT)) at 12 months of age

#### 7.1.2 Secondary study parameters/endpoints

##### *Pneumococcal serotypes*

- Opsonophagocytoses immediately before and 7-9 days after the booster at 11-months of age
- Avidity at 5, 8, immediately before and 7-9 days after the booster at 11-months and at 12 months of age
- Antibody concentrations and geometric mean concentrations (GMT) at 5, 8, immediately before and 7-9 days after the booster at 11-months and at 12 months of age
- Kinetics of antibody concentrations and geometric mean concentrations (GMT) over time (at 5, 8, 11 and 12 months of age)

##### *DTaP-Hib*

- Antibody concentrations and geometric mean concentrations (GMT) at 5, 8, 11 and 12 months of age

#### 7.1.3 Other study parameters

Date of birth, gender, duration of pregnancy, birth weight, duration of breast feeding, use of day care, family members and age, smoking habits parents, use of antibiotics last 3 months, current symptoms of cold, ear infections, other disorders.

PCV13 groups: painkiller use around vaccination.

### 7.2 Randomisation, blinding and treatment allocation

Two randomization lists will be made, one for group 1 and one for group 2.

Prior to starting the trial (group 1) and prior to the 11 month visit (group 2) envelopes which contain a letter indicating allocation to one of the sub groups will be numbered in

random order using a random number generator ([www.random.org](http://www.random.org)). The envelopes will be sealed by the principal investigator (who will not be involved in randomization visits) and given to the study team. For group 1 during visit 1, after eligibility has been confirmed and the informed consent form has been signed, the study team member should open the envelope with the lowest number still available. The volunteer will be assigned to the group indicated in the letter. For group 2 the randomization will take place before the 11 months home visits.

In case replacements are warranted due to premature withdrawal of volunteers, after all envelopes have been used, the sponsor will prepare a new set of sealed and randomly numbered envelopes corresponding to the number of required replacements.

For group 1 at the time of randomization of a subject the study team member should take the investigational product vial and vaccinate the subject with the product(s) as indicated. The treatment number should be recorded in the CRF.

The study will not be blinded.

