**Study design:**

A controlled randomized intervention trial with 2 groups (see figure 2 and table 1).

- Group 1 PCV13
  - Divided in group 1a and 1b; 33 infants per group
- Group 2 PCV10
  - Divided in group 2a and 2b; 33 infants per group

Group 1 and 2 are split in sub groups in order to reduce the burden of the 8 ml blood samples. Randomization will be done within group 1 and within group 2.

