### 3. STUDY DESIGN

Children eligible to receiving the regular vaccinations of the NIP, born after August 2011 (assuring that all children are eligible for and will receive Hepatitis B vaccination)

A controlled, randomized, intervention trial with 2 groups (see figure 2 and table 1).

- Children of group 1 will be invited first (around the age of 1 month), since they have to receive all DTaP-IPV-Hib-HepB and PCV13 vaccinations as part of the trial
  - Vaccinations will be given during home visits
  - Children will be randomized over 2 sub groups in order to diminish the burden of the 8 ml blood sample (which is collected just before or 7-9 days after the 11-months vaccination)
  - For the immune memory, collect 33 children per sub group in order to have 25 evaluable children per sub group (sub group 1a and 1b)
  
- Children of group 2 will be invited around the age of 3.5 months, as to include them in the trial at the age of 5 months
  - Vaccinations are not part of the trial, since they already receive them during well-baby clinic visits
  - Children will be randomized over 2 sub groups in order to diminish the burden of the 8 ml blood sample (which is collected just before or 7-9 days after the 11-months vaccination)
  - For the immune memory, collect 33 children per sub group in order to have 25 evaluable children per sub group (sub group 2a and 2b)

Randomization will be done within group 1 and separately within group 2.

The randomization will not be done for the total study (group 1 and 2 together) since children of the PCV10 group already receive all proper vaccinations in the NIP and randomization would result in a long period between invitation at 1 month of age and inclusion at 5 months of age for the PCV10 group.

Figure 2 Study schedule

[figure not shown]

Blood samples (8 ml) are used for cellular immunogenicity (and 100 ul, of these samples will be used for humoral immunogenicity). Blood samples (100 ul) are used for humoral immunogenicity.

|                                                                                                                               | Group
1a
(PCV13) | Group
1b
(PCV13) | Group
2a
(PCV10) | Group
2b
(PCV10) |
|-------------------------------------------------------------------------------------------------------------------------------|------------------------|------------------------|------------------------|------------------------|

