| Invitation (~September 2011)                                                                                                  | x                      | x                      |                        |                        |
| Invitation (~Januari 2012)                                                                                                    |                        |                        | x                      | x                      |
| Receive response card                                                                                                         | x                      | x                      | x                      | x                      |
| Send extra information by email                                                                                               | x                      | x                      | x                      | x                      |
| Telephone call 1 (inquire about the parents interest, explain the study if necessary, make an appointment)                    | x                      | x                      | x                      | x                      |
| Send the extra information also on paper                                                                                      | x                      | x                      | x                      | x                      |
| Check with RCP if child is allowed to receive vaccinations                                                                    | x                      | x                      |                        |                        |
| 2 months vaccination (PCV13 and DTaP-IPV-Hib-HepB)
Including check in- exclusion criteria, signing of IC and randomization | x                      | x                      |                        |                        |
| 3 months vaccination (PCV13 and DTaP-IPV-Hib-HepB)                                                                            | x                      | x                      |                        |                        |
| 4 months vaccination (PCV13 and DTaP-IPV-Hib-HepB)                                                                            | x                      | x                      |                        |                        |

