| 5 months blood collection (heel/finger stick)
Including check in- exclusion criteria, signing of IC                        |                        |                        | x                      | x                      |
| 8 months blood collection (heel/finger stick)                                                                                 |                        |                        | x                      | x                      |
| Randomization                                                                                                                 |                        |                        | x                      | x                      |
| Pre 11 months blood collection (8 ml) Questionnaire                                                                           |                        |                        | x                      |                        |
| Pre 11 months blood collection (heel/finger stick) Questionnaire                                                              |                        |                        |                        | x                      |
| Pre 11 months blood collection (8 ml) & vaccination (PCV13 and DTaP-IPV-Hib-HepB) Questionnaire                               | x                      |                        |                        |                        |
| Vaccination (PCV13 and DTaP-IPV-Hib-HepB) Questionnaire                                                                       |                        | x                      |                        |                        |
| Post 11 months blood collection (7-9 days) Questionnaire                                                                      |                        | x                      |                        | x                      |
| 12 months blood collection (heel/finger stick)                                                                                | x                      | x                      | x                      | x                      |
| End of study for participants                                                                                                 | x                      | X                      | x                      | x                      |

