#### 4.4 Sample size calculation

For **cellular immunity**: each group will contain 25 evaluable children (based on previous experience we expect to include at least 30 children in order to reach 25 evaluable children). The group size is based on the previous KOKKI study (NL24329.000.08).

*'The clinical meaning of differences between the numbers of memory B-cells is still unknown. Therefore power calculations are at the moment not possible. Previous research has shown that the number of memory-B cells circulating in blood is very low before a booster vaccination and in order to observe a trend after revaccination a group of 22 children is needed (including a possible 10% loss of subjects' leads to 25 children for each group).'*

In the KOKKI study, for each child blood was collected at one time point only, being either pre- or 7-9 days post-booster. Inclusion and blood collection was during the same visit. Inclusion in the current study however starts at first vaccination, respectively 9 (group 1) and 6 (group 2) months prior to blood collection for cellular immunity, which can lead to a higher amount of dropout. Taking into account a 10% dropout up to 11 months, we included 33 children in each group. A subsequent estimated failure rate to collect sufficient blood cells of 15% will generate 25 evaluable children.

**Antibody concentrations** will be compared between the PCV10 group of the current study and the PCV13 group of the PIM study (vaccination schedule 2, 3, 4 and 11 months) at 12 months after vaccination. As significance level we take 0.05 two-sided and as power 80%. The expected variance of log(GMC) is 0.27 (this is for serotype 6B, the serotype with the highest variance). Using the following formula  $n = 2k^2\sigma^2 / \delta^2$ , we need 47 children per group to detect a 2-fold difference in GMC (=0.30 difference in log(GMC)) between the two groups. A 2- to 2.5-fold difference is considered to represent a true difference in immunogenicity in this type of study (8,9). To account for 20% dropout, 59

children need to be included per group. As we already include  $2 \times 33 = 66$  children in the cellular immunity part of the study, this group is also large enough to assess antibody concentrations.

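### Group 1 is randomised to sub groups 1a and 1b at 2 months although the allocation first acts at 11 months, leaving avoidable dropout after allocation

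*Protocol*

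**What the plan says.** Section 7.2 of the protocol sets two different times for the same kind of split. In group 1 the envelope is opened early: "For group 1 during visit 1, after eligibility has been confirmed and the informed consent form has been signed". In group 2 it is opened late: "For group 2 the randomization will take place before the 11 months home visits". Table 1 in section 3 agrees. The 2-month vaccination row for 1a and 1b carries the note "Including check in- exclusion criteria, signing of IC and randomization", while the group 2 randomisation row stands between the 8-month and 11-month samples.

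The split concerns only the timing of the 8 ml sample, "which is collected just before or 7-9 days after the 11-months vaccination" (section 3), and the Summary gives its purpose: "Group 1 and 2 are split in sub groups in order to reduce the burden of the 8 ml blood samples". In Table 1, sub groups 1a and 1b have the same events at 2, 3 and 4 months. They first part at 11 months, where 1a has "Pre 11 months blood collection (8 ml) & vaccination (PCV13 and DTaP-IPV-Hib-HepB) Questionnaire" and 1b is vaccinated without that sample. Sub group 1b then has the entry "Post 11 months blood collection (7-9 days) Questionnaire", which 1a does not.

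Section 4.4 puts nine months between group 1 inclusion and the cellular sample, recognises that this may increase dropout, and allows for it: "Taking into account a 10% dropout up to 11 months, we included 33 children in each group". Section 7.2 states that the study is not blinded. Section 7.5 rules out replacing group 1 children once all the 2-month vaccinations have been given.

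**The concern.** Plasma and memory B cells before and 7-9 days after the booster are a main endpoint (section 7.1.1). Each child gives the 8 ml sample once, so the change across the booster within PCV13 is read by comparing different children, 1a against 1b. That reading needs the two sub groups to be exchangeable at 11 months.

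Randomising when the allocation takes effect secures this up to that visit. Randomising nine months earlier, without blinding and with one sub group facing an additional visit, lets dropout that depends on the allocation alter the size and mix of 1a and 1b before either has contributed a cellular result. Losses after the 2-month vaccinations cannot be replaced. The protocol explains why groups 1 and 2 are not randomised together, but not why group 1 is split so early.

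**Working it through.** **Inputs.** 33 children per sub group, 66 in group 1; 10% dropout up to 11 months; 15% failure to obtain enough cells; target of 25 evaluable, derived from 22 needed plus 10% loss (all section 4.4). Envelopes are numbered in random order and the lowest number remaining is opened (section 7.2).

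**1. The plan's figure.** 25 / (0.90 × 0.85) = 32.7, rounded up to 33. Forward: 33 × 0.90 × 0.85 = 25.2. The 33 per sub group reproduces. Likewise 22 / 0.90 = 24.4, rounded up to 25.

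**2. Children exposed to the problem.** 66 × 0.10 = 6.6 expected losses, 3.3 per sub group, between allocation and the first visit at which it matters. With randomisation just before 11 months this is about 0, and the expected numbers are unchanged: 66 × 0.90 = 59.4 remaining, 29.7 per sub group, 29.7 × 0.85 = 25.2 evaluable.

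**3. Chance imbalance if dropout ignores the allocation.** The children retained in each sub group follow Bin(33, 0.90). The difference between sub groups has SD √(2 × 33 × 0.10 × 0.90) = 2.4. P(difference of 3 or more) = 0.30; P(4 or more) = 0.15.

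**4. Chance that both sub groups reach a target,** by exact binomial calculation, under three procedures:
- *Early (as written):* evaluable per sub group ~ Bin(33, 0.765), and both must reach the target.
- *Late, same 66 envelopes:* N ~ Bin(66, 0.90) remain, their split is hypergeometric (33 of each letter among 66), then 15% cell failure.
- *Late, balanced list:* N ~ Bin(66, 0.90), split evenly, then 15% cell failure.

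| Procedure | Both ≥ 25 | Both ≥ 22 |
|---|---|---|
| Early | 0.400 | 0.871 |
| Late, same 66 envelopes | 0.400 | 0.871 |
| Late, balanced list | 0.443 | 0.903 |

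The first two rows are identical because, when dropout is independent of the letter, it makes no difference to the numbers whether the letter is read before or after the dropout. The gain comes from the even split. For other dropout rates (assumed), both ≥ 25 moves from 0.689 to 0.714 at 5%, and from 0.168 to 0.202 at 15%.

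**5. Illustration of differential dropout (assumed; the protocol gives no such figures).** With 5% dropout in 1a and 15% in 1b, 33 × 0.95 = 31.4 and 33 × 0.85 = 28.1 children remain, and 31.35 × 0.85 = 26.6 and 28.05 × 0.85 = 23.8 are evaluable. The second figure is below 25 but above the 22 that section 4.4 says is needed.

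**The case against.** The other side has a good deal right.

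- **Sample size.** A reader might infer that 33 per sub group is inadequate because of the timing. It is not: dropout is already allowed for, and the arithmetic reproduces. The chance of both sub groups reaching 25 is low because 25.2 expected leaves almost no margin, whenever the envelope is opened.
- **Source of the gain.** A reader might credit the move from 40% to 44% to later randomisation. The calculation shows that it belongs to the balanced list.
- **Differential dropout.** Nothing in the protocol shows that knowing the sub group drives dropout. Both sub groups have one 8 ml sample and one heel or finger stick, and section 4.4 expects the burden to be seen as relatively low. It is also an inference that parents know the allocation for nine months: a team member opens the envelope at the home visit of an unblinded study, but the text does not say that parents are told then.
- **Loss at the post-booster visit.** Any loss tied to 1b's extra visit after the booster follows allocation under either timing. Later randomisation does not remove it.
- **Comparability with group 2.** A reader might infer that the early split makes 1a and 1b selected differently from 2a and 2b. Groups 1 and 2 already differ by design in age at entry, recruitment rate and region, and they are not randomised against each other. The change does not alter that.
- **No benefit.** That early randomisation serves no purpose is also inferred, since the protocol is silent. An operational reason may exist. Group 2 does show that late randomisation is workable in this trial.

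What remains is that dropout up to 11 months falls after allocation when it need not.

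**Conclusion.** The point holds as a minor improvement to the design. Group 1 is allocated nine months before the allocation has any effect. About 6.6 of 66 children are expected to be lost in between if the protocol's 10% is right, and in an unblinded study that loss could differ between 1a and 1b. This opens an avoidable route to bias in the unpaired pre/post-booster B-cell contrast within PCV13. The size of any such bias cannot be derived from the document, and the 5% versus 15% case is only an illustration.

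The PCV10 versus PCV13 contrast is non-randomised either way, and the 12-month antibody sample is taken in both sub groups, so both are little affected. With a balanced list at 11 months, the chance that both sub groups reach 25 evaluable rises from 40% to 44%, and that both reach 22 from 87% to 90%. These figures assume independent losses at the protocol's rates and no replacement; section 7.5 permits replacement only until the 2-month vaccinations are complete, which would slightly reduce the losses counted here.

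**What to change.** - In section 7.2, randomise group 1 just before the 11-month visit, as for group 2. Use a list prepared at that time, balanced or blocked 1:1, for the children still in the study. Reusing the 66 envelopes would remove the exposure to differential dropout before 11 months but would not improve the balance of numbers.
- In Table 1, move the group 1 randomisation entry from the 2-month row to a row just before the 11-month visit.
- In section 7.2, separate the sentence about taking the vial and vaccinating from the act of randomisation. Sub groups 1a and 1b receive the same vaccines, so the allocation letter has no bearing on it.
- Report dropout by sub group, including loss between the 11-month visit and 1b's sample at 7-9 days, which stays after allocation under either timing.

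If there is an operational reason for the 2-month allocation, state it and keep the reporting by sub group. The cost is wording in section 7.2 and Table 1 and one new list, with no extra child, visit or sample.
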